# Abbreviations

| ABP | Arterial blood pressure |
| --- | --- |
| ABPd | Diastolic arterial blood pressure |
| AIC | Akaike information criterion |
| ADF | Augmente Dickey-Fuller |
| ANOVA | Analysis of variance |
| ARIMA | Autoregressive integrative moving average |
| ASIA | American Spinal Injury Association |
| CCF | Cross Correlation Function |
| CRF | Case report form |
| CT | Computed tomography |
| FIM | Functional Independence Score |
| HSC | Health Sciences Center |
| IRF | Impulse response function |
| KPSS | Kwiatkowski–Phillips–Schmidt–Shin |
| LL | Log likelihood |
| SICU | Surgical Intensive Care Unit |
| ISP | Intraspinal pressure |
| MAP | Mean arterial pressure |
| PI | Principal Investigator |
| POD | Post-operative day |
| QLI-SCI | Quality of Life Index for Spinal Cord Injury |
| RAP | Cerebral compensatory reserve index |
| REB | Research ethics board |
| SAE | Serious Adverse Events |
| sAMP | Pulse amplitude of intraspinal pressure |
| sPAx | Spinal pulse amplitude index |
| sPRx | Spinal pressure reactivity index |
| sRAP | Intra-spinal compensatory reserve |
| SCPP | Spinal cord perfusion pressure |
| SLICS | Subaxial Cervical Spine Injury Classification and Severity Scale |
| TLICS | Thoracolumbar Injury Classification Score |
| VARIMA | Vector autoregressive integrative moving average |

# Protocol Summary

| Title | Intraspinal Pressure Monitoring for Acute Traumatic Spinal Cord Injury: A Validation Study |
| --- | --- |
| Objectives | The primary objective of this study is to validate the methodology of invasive intraspinal pressure monitoring to derive parameters for optimal spinal cord perfusion pressure, spinal cord reserve capacity and spinal reactivity index using data obtained during the patient’s SICU stay.Secondary objectives of this study will be to a) evaluate the safety of invasive intraspinal pressure monitoring, b) prospectively evaluate the overall relationship between spinal cord perfusion pressure and functional outcomes in patients with acute traumatic spinal cord injury and c) evaluate the relationship between spinal cord perfusion pressure, motor evoked potentials and functional outcomes after *incomplete* spinal cord injury. |
| Population | Adult (age 18-75) patients admitted with ASIA grade A, B, or C acute traumatic spinal cord injury |
| Number of Sites | Health Sciences Center |
| Study Duration | 3 years |
| Subject Participation Duration | 1 year |
| Estimated Time to Complete Enrollment | 2yrs |

## Introduction: Background and Rationale

Acute traumatic spinal cord injury has devastating consequences for patients and their families. In North America, the incidence of acute traumatic spinal cord injury is estimated to be 40 per million people1. To date, clinical research efforts have been focused on limiting the degree of secondary injury by performing spinal decompression2 and optimizing spinal cord perfusion early after the traumatic event.

Optimizing blood flow to the spinal cord has been an ongoing area of research for decades3. The objective of improving blood flow to the spinal cord is to reduce the area of ischemia around the site of injury thereby reducing axonal loss and necrosis4. Numerous animal studies have been conducted to evaluate the effects of blood flow manipulation on spinal cord function5. Historically, a variety of models were used to induce spinal cord injury with significant heterogeneity in the mechanism of injury. Similarly, significant heterogeneity exists with respect to measurement of outcomes where some studies observed changes in spinal cord blood flow whereas others have documented changes in neurological function6. However, these studies have several limitations. Many of these studies manipulated blood pressure over short periods of time and similarly evaluated functional outcomes within a very short time period following the spinal cord injury.

Similarly, data in humans regarding manipulation of blood pressure in the management of spinal cord injury is limited. A prior systematic review performed at our institution6 identified 2 prospective studies and 7 retrospective studies that analyzed the relationship between hypertensive therapy and functional outcome in acute traumatic spinal cord injury. Amongst these studies, no clear relationship could be made between hypertensive therapy and functional outcomes in patients with traumatic spinal cord injury. Despite the paucity of data, current North American guidelines suggest maintaining mean arterial pressure between 85–90mmHg for 5–7 days after initial injury7.

Recently, researchers at the University of Cambridge have described the use of an intraspinal pressure monitor to better define spinal cord perfusion pressure8. In their preliminary observational study, the authors described the placement of a fiberoptic pressure monitor placed into the subarachnoid space directly at the site of spinal cord injury. Intraspinal pressure readings were then recorded above, below and at the site of injury. The authors then defined the components of the intraspinal waveform and correlated these components to patients’ respiratory rate, heart rate and opening of the aortic valve. Attempts at manipulating the intraspinal pressure through hyperventilation and osmotic agents were deemed unsuccessful though use of vasopressors seemed to improve spinal cord perfusion pressure. In other reports, the authors successfully characterized correlation coefficients defining the reserve capacity of the spinal cord and autoregulatory curves for spinal cord perfusion pressure. In doing so, the authors were able to derive an optimal spinal cord perfusion pressure based on recordings directly from the site of injury. In whole, this work represents the most direct and complete evaluation of the relationship between mean arterial pressure, intraspinal pressure and spinal cord perfusion pressure in humans.

Despite the elegance and significance of this work, the methodology has not been validated in any other institution to date. We aim to be the first group to validate the methodology of intraspinal pressure monitoring.

## Objectives

### ***Study Objectives***

The primary objective of this study is to validate the methodology of invasive intraspinal pressure monitoring to derive parameters for optimal spinal cord perfusion pressure, spinal cord reserve capacity and spinal reactivity index using data obtained during the patient’s SICU stay (or a maximum of 5 days after injury). The following specific aims will be achieved through the primary objective:

1. The temporal profile of intra-spinal pressure (ISP) and arterial blood pressure (ABP) over the course of the patient’s SICU stay will be characterized, assessing the time series behaviors of ISP and ABP, and by determining the spinal cord perfusion pressure (SCPP) as: ABP – ISP.
   1. HYPOTHESIS: ISP, ABP and SCPP will demonstrate a reproducible relationship in time both within and between patients, allowing for comment on the transmission of ABP pulsations to pulsatile spinal cord blood volume.
2. Feasibility of intra-compartmental compensatory reserve will be characterized, by evaluating the relationship between slow-wave vasogenic fluctuations in the Fast Fourier Transformed pulse amplitude of ISP (called sAMP) and ISP over time.
   1. HYPOTHESIS: It will be possible to derive a continuous metric of intra-spinal compensatory reserve (called sRAP), which represents aspects of intra-spinal compliance and will demonstrate a negative parabolic relationship to continuously measured ISP. This will mimic that seen between intra-cranial pressure and continuously measures cerebral compensatory reserve index, call RAP.
3. Spinal cord vascular reactivity will be characterized continuously using the relationship between slow-wave vasogenic fluctuations in ISP or sAMP, and either mean arterial pressure (MAP) or SCPP.
   1. HYPOTHESIS A: These spinal cord vascular reactivity indices will display characteristic parabolic relationships with MAP and SCPP, and positive correlations to progressively increasing ISP and sAMP.
   2. HYPOTHESIS B: The minimum of the parabolic relationship between spinal cord vascular reactivity metrics and MAP or SCPP will allow for continuously derived individual ‘optimal’ SCPP and ‘optimal’ MAP.

Secondary objectives of this study will be to:

1. Evaluate the safety of invasive ISP monitoring.
   1. HYPOTHESIS: Invasive intra-spinal pressure monitoring will be safe and feasible, with low complication rates.
2. Prospectively evaluate the overall relationship between spinal cord perfusion pressure and functional outcomes in patients with acute traumatic spinal cord injury.
   1. HYPOTHESIS: There will be a general positive relationship between both SCPP and individual optimal SCPP, with patient functional outcome in acute traumatic spinal cord injury.
3. Evaluate the relationship between SCPP, motor evoked potentials and functional outcomes after *incomplete* spinal cord injury.
   1. HYPOTHESIS: Time spent with SCPP near individual optimal SCPP will be directly associated with improved motor evoked potentials and functional outcomes in *incomplete* spinal cord injury.

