## 4. Study Design

### **4.1 Patient Population**

This study will be a single-center observational study involving patients admitted to the intensive care unit at Health Sciences Centre with acute traumatic spinal cord injury (ASIA A, B or C). All patients will undergo placement of an intraspinal pressure monitor within 24hrs of arrival. Physiological recordings will occur during the SICU stay for a maximum duration of 5 days (or until discharge from the intensive care unit).

Given that this is a feasibility and validation study, we will recruit patients over 2 years and anticipate that 20 patients will be enrolled during this time frame. Upon admission, patients will be screened for inclusion in the study based on the inclusion and exclusion criteria listed in *Section 5*. Initial demographic information, medical history, physical examination and imaging findings will be recorded using standardized data collection forms for all patients that consent to participation in the study. Patients will then be taken for surgical intervention within 24hrs of admission, and an intraspinal pressure monitor will be inserted as part of the overall surgical procedure. Initial intraspinal pressure readings will be recorded intraoperatively. Standardized data collection forms will then be used to collect pertinent data related to the surgical intervention and any intraoperative adverse events. Similarly, postoperative adverse events will be collected for the first 30 days following surgical intervention.

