### **4.2 Physiologic Data Capture and Processing**

Once surgical intervention has been completed, the patient will be monitored in the intensive care unit as long as deemed necessary by care providers. During this time in SICU, intraspinal pressure and physiological parameters such as heart rate, respiratory rate, blood pressure, and mean arterial pressure will be captured at the bedside using a secure laptop with ICM+ software.

Both ABP and ISP will be obtained through invasive methods, with all signals recorded in high-frequency time series, sampled at 100 Hz or higher through and analogue to digital signal converters (DT9804 or 9T9826; Data Translations, Marlboro, MA), using ICM+ software (Cambridge Enterprise Ltd, Cambridge, UK, http://www.neurosurg.cam.ac.uk/icmplus) connected to our SICU monitors. Signals from all of the monitoring devices described below are subsequently recorded in time series using this software over the course of the recording periods described above. All physiologic signals from monitoring devices within the SICU for neurologically ill patients are currently recorded and archived as part of a separate prospective signal database study that will be ongoing at HSC (HS20840; H2017:181). Arterial blood pressure (ABP) will be obtained through either radial or femoral arterial lines connected to pressure transducers (Baxter Healthcare Corp. CardioVascular Group, Irvine, CA). ICP will be acquired via an intra-parenchymal strain gauge probe (Codman ICP MicroSensor; Codman & Shurtleff Inc., Raynham, MA).

Post-acquisition processing of the above signals will be conducted using ICM+ software. SCPP will be calculated using the formula: SCPP = MAP – ISP. Systolic ABP (ABPs) will be determined by calculating the maximum ABP over a 1.5 second window, updated every second. Similarly, diastolic ABP (ABPd) will be determined by calculating the minimum ABP over a 1.5 second window, updated every second. Pulse amplitude of ISP (sAMP) will be determined by calculating the fundamental Fourier amplitude of the ICP pulse waveforms over a 10 second window, updated every 10 seconds.

Ten-second moving averages (updated every 10 seconds to avoid data overlap) will be calculated for all recorded signals: ISP, ABP (which produced MAP), ABPs and ABPd. Ten-second moving averages will be calculated in order to focus on slow waves of parent signals, decimating the frequency to the range associated with vascular autoregulation.

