## 8. Statistical Considerations

### 8.1 General Statistics

Statistical analysis will be performed utilizing R statistical software (R Core Team (2018). R: A language and environment for statistical computing. R Foundation for Statistical Computing, Vienna, Austria. URL https://www.R-project.org/). Alpha for statistical significance will be set at 0.05, with normality for all continuous variables tested via Shapiro-Wilks test. Basic descriptive statistics will be performed, with comparison between groups and variables conducted via t-test, Mann-Whitney-U, chi-square, analysis of variance (ANOVA), Kruskal-Wallis, Friedman and Joncheere-Terpstra testing, where appropriate. General correlations will be described using Pearson/Spearman coefficients, where applicable.

Descriptive statistical analysis of the relationships between physiologic variables will be facilitated through various error bar plots, linear models, quadratic models (ie. For optimal SCPP determination) and locally weighted scatterplot smoothing (LOESS) techniques, depending on the physiologic relationship being assessed.

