### 8.3 Association with Secondary Outcomes

ISP, MAP, SCPP, sAMP, sRAP and the spinal vascular reactivity indices will be evaluated in relationship to motor evoked potential recordings, and functional outcome measures at the defined time periods of assessment. Such analysis will involve linear and logistic regression modelling techniques, evaluating the relationship between the physiologic parameters with: ASIA, FIM and QLI-SCI functional outcome metrics.

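### Time with SCPP near the individual optimum also reflects how variable SCPP is, so a positive result for secondary hypothesis 3 cannot by itself show that the optimum matters

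*Protocol*

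**What the plan says.** The exposure and the claim are set in the Protocol, Study Objectives, secondary objective 3: "Time spent with SCPP near individual optimal SCPP will be directly associated with improved motor evoked potentials and functional outcomes", restricted to incomplete injury. The optimum comes from the patient's own recording. Under aim 3, hypothesis B, "The minimum of the parabolic relationship between spinal cord vascular reactivity metrics and MAP or SCPP will allow for continuously derived individual" optima of SCPP and MAP. In section 4.2, "SCPP will be calculated using the formula: SCPP = MAP – ISP".

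SCPP is observed and not assigned: "This study will be a single-center observational study involving patients admitted to the intensive care unit" (section 4.1). The same section expects 20 patients in total across ASIA A, B and C, and says that "Physiological recordings will occur during the SICU stay for a maximum duration of 5 days".

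Section 8.1 says "Alpha for statistical significance will be set at 0.05" and does not give sidedness. Section 8.3 states that "ISP, MAP, SCPP, sAMP, sRAP and the spinal vascular reactivity indices will be evaluated in relationship to motor evoked potential recordings" and to functional outcome, by linear and logistic regression. Neither time near the optimum nor SCPP variability is among the predictors listed there. The protocol gives no band for 'near', no SCPP SD, and no figure for how far patients' mean SCPP lies from their optimum.

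**The concern.** Two patients whose mean SCPP sits exactly at their optimum can differ widely in time near it, only because one has a steadier SCPP. Injury severity, injury level or complications could plausibly make SCPP less stable and also worsen outcome. The design does not control stability. If stability alone drives recovery, time near the optimum can still correlate with outcome, and so could time near any central value, including the patient's own average.

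Hypothesis 3 is where the protocol links time near the individual optimum to outcome. A positive result read as evidence for the optimum could lend unearned support to individualised targets.

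**Working it through.** The protocol states no power, effect size or SCPP SD, so it has no figure of its own to reproduce. The mechanism is checked directly.

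**1. Formula.** Let SCPP within a patient be normal with SD s and mean at distance d from the optimum. The share of time within ±w of the optimum is Φ((w − d)/s) − Φ((−w − d)/s).

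- d = 0, w = 5 mmHg: s = 6 gives 2Φ(0.833) − 1 = 60%; s = 15 gives 2Φ(0.333) − 1 = 26%.
- d = 0, w = 10 mmHg: s = 6 gives 90%; s = 15 gives 50%.
- d = 20, w = 10 mmHg: s = 6 gives Φ(−1.667) − Φ(−5) = 5%; s = 20 gives Φ(−0.5) − Φ(−1.5) = 24%.

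Spread alone moves the exposure about two-fold when the patient is centred on the optimum. For a patient far from it, the direction reverses.

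**2. Which component dominates.** Assumptions, none from the protocol: median SCPP SD 9 mmHg with log-SD 0.3 between patients; offsets d normal with mean 0 and independent of SCPP SD; band ±5 or ±10 mmHg. Rank correlations of time near the optimum:

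| SD of offsets (mmHg) | with SCPP SD | with distance from optimum |
|---|---|---|
| 5 | -0.71 to -0.78 | -0.50 to -0.55 |
| 8 | -0.40 to -0.49 | -0.77 to -0.80 |
| 10 | -0.26 to -0.35 | -0.85 to -0.88 |

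At offset SD 3 the correlation with SCPP SD is -0.93 to -0.95. The lead passes from spread to distance somewhere between offset SD 5 and 8 mmHg. With SCPP SD uniform on 8-15 mmHg and a ±10 band, the variance share due to SCPP SD tells the same story: 91%, 57%, 17%, 8% and 1% at offset SD 3, 5, 8, 10 and 15.

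**3. False support.** Outcome is made to depend only on stability (correlation 0.5 with standardised log SCPP SD) and not on the optimum. The test is two-sided at 0.05 (sidedness assumed), counting only positive associations, so the nominal rate is 2.5%. The protocol does not size the incomplete-injury subset; 10 is assumed. All else is as in step 2.

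| SD of offsets (mmHg) | false support, n = 10 |
|---|---|
| 3 | 28-30% |
| 5 | 18-22% |
| 8 | 9-11% |
| 10 | 6-7% |
| 15 | 3-4% |

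A second set of assumptions (SCPP SD uniform on 6-18, band ±10, outcome correlation -0.6 with SCPP SD) gives 36%, 14% and 7% at offset SD 5, 10 and 15 with n = 10, and 49%, 16% and 8% with n = 13.

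**4. Estimated optimum.** Take a quadratic fit to 5 days of minute data when there is no true optimum (flat curve). A minimum inside the patient's range is still found in about 44% of patients. Among them time near it still has rank correlation -0.57 to -0.59 with SCPP SD.

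**5. After the fix.** Conditioning on SCPP SD, or on time in the same band around the patient's own mean, brings false support back to about 2-3% in the scenarios run.

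**The case against.** The strongest reply is that distance may well dominate. Taking the optimum from the patient's own record keeps it within the range visited but does not place it near the mean. At offset SD 8 mmHg distance already leads, and at 15 false support is close to nominal. That stable patients do better, and by how much, is also assumed. All of this stands, and it limits the size of the point.

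A reader might infer that time near the optimum is largely a measure of variability. The documents do not support that, because they give no SCPP SD, offset or band. A reader might also compute false support with all 20 patients, which is higher. That would need every enrolled patient to have an incomplete injury, while ASIA A is eligible.

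The hypothesis claims only association, in an observational feasibility study, and the band and covariates may properly sit in a statistical analysis plan that is not shown. So the silence of section 8.3 on adjustment is not an error. What remains is that the exposure named in the hypothesis mixes two explanations, and a positive result will naturally be read as favouring one of them.

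Finally, excursions from the optimum are part of the exposure if the optimum matters. Replacing the exposure with the distance between mean SCPP and the optimum would score wide swings around the optimum as ideal. That objection stands, which is why the exposure should be kept and supplemented. It also means that conditioning on spread may remove some real signal.

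**Conclusion.** The point holds in a conditional form. Time near the optimum combines closeness with stability, and hypothesis 3 can be supported when only stability matters. With 10 incomplete injuries, SCPP SD about 9 mmHg and a stability-outcome correlation of 0.5, false support runs from 28-30% at offset SD 3 mmHg down to 3-4% at 15, against 2.5% nominal. It is serious if patients' mean SCPP usually lies within about 5 mmHg of their optimum and minor if offsets are 10 mmHg or more. The protocol does not allow a choice between these cases. The mechanism is arithmetic; the SD, offsets, band, subset size and stability effect are all assumptions. The point concerns how one secondary hypothesis will be interpreted and leaves the primary objective untouched.

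**What to change.** Keep time near the optimum as the exposure in hypothesis 3, and name it in section 8.3. In both places add that it will be reported beside (a) the patient's SCPP SD and (b) the time within the same band around the patient's own mean SCPP. Show the association with outcome alone and conditional on one of these, chosen in advance, and give the mean-to-optimum distance as a supporting measure.

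State the reading rule: an association is attributed to the individual optimum only if it exceeds that for time near the patient's own mean or persists given SCPP SD. 'Exceeds' is best judged with both times in one model, since two point estimates from so few patients can differ by chance. If the optimum is updated over time, compute the patient's own mean over the same window.

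The cost is a few derived variables from signals already recorded and a sentence or two in each section. The downside is precision: with 20 or fewer patients the conditional estimate will have a wide interval, so failure to persist is not evidence that the optimum is irrelevant.

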### ***3.2* Study Outcome Measures**

*Primary Outcome Measures*

The outcome measures of interest for our primary objective and specific aims include monitoring of intraspinal pressure via a strain-gauge pressure transducing wire placed at the site of injury and the derivation of various spinal physiologic metrics (see section 4.1 in Study Design). We will focus on various signal processing techniques to derive: ISP, MAP, SCPP, sAMP, sRAP and various spinal cord vascular reactivity metrics during the post-acquisition processing phase of the study. This will allow for the evaluation of relationships between spinal physiologic metrics, as outlined in the specific aims for the primary objective.

*Secondary Outcome Measures*

Safety of intraspinal pressure monitoring will be measured based on the accuracy of placement of the probe from postoperative computed tomography (CT) scan imaging, as well as collection of adverse events including infection rates, rates of pseudomeningoceles, neurological injury, probe dislodgement, meningitis, and/or subdural hematoma at the site of probe placement.

Where functional outcomes are of interest, we will measure changes to the ASIA impairment scale, functional independence score (FIM) and Quality of Life Index for Spinal Cord Injury (QLI-SCI).

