### ***4.3* Motor Evoked Potentials**

In patients undergoing evaluation for motor evoked potential monitoring, we will capture transcranial magnetic motor evoked potentials within the 24 hours pre-operatively, 24hrs post-operatively and again during the standardized functional assessments at 1, 3, 6, 9 and 12 months.

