***4.4 Functional Outcome Assessments***

Each patient will then undergo standardized functional assessments at 1, 3, 6, 9, and 12 months following the acute injury. Functional assessments will include assessment of the ASIA impairment scale, functional independence score (FIM) and Quality of Life Index for Spinal Cord Injury (QLI-SCI). We may also use information captured in the Rick Hansen Spinal Cord Injury Registry, which is a national database that collects functional outcomes and adverse events on patients with traumatic spinal cord injury. This registry is currently approved by the University of Manitoba Research Ethics Board (Ethics # H2005:173(HS14502)).

**5.** Study Enrollment and Withdrawal

In this study, we aim to enroll 20 patients over the course of 2 years to evaluate the role of intraspinal pressure monitoring in the management of acute spinal cord injury. As described above, patients with acute traumatic spinal cord injury will be identified at the time of admission to the Health Sciences Center.

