***5.1 Inclusion Criteria***

In order to participate in this study, patients must meet all of the following criteria:

- patients with acute traumatic spinal cord injury ASIA A, B or C
- spinal vertebral level between C0-L1
- age between 18–70yrs

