**Baseline Enrollment Visit (Day 0 to Day 1)**

After obtaining consent, study personnel will:

- perform an initial clinical assessment to obtain patient’s medical history
- conduct a physical examination
- verify medications and document laboratory investigations
- record vital signs for the patient
- review clinical exam and radiographic imaging studies to derive injury classification score using TLICs or SLICs scoring systems (all patients will need CT scan of spine and MRI of spine within first 24hours of arrival to SICU)
- administer ASIA impairment scale assessment (an objective scoring system to document level of spinal cord injury)
- administer patient questionnaires including Functional Independence Score and Quality of Life Index for Spinal Cord Injury (QLI-SCI)

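### The only clinical-examination neurological outcome named is the ASIA impairment grade, which cannot worsen in grade A patients and misses change within a grade; ASIA motor and sensory scores and level are not specified

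*Protocol*

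**What the plan says.** Section 3.2 sets out the functional outcomes: "we will measure changes to the ASIA impairment scale", together with FIM and QLI-SCI. Section 4.4 repeats the list for follow-up: "Functional assessments will include assessment of the ASIA impairment scale, functional independence score (FIM) and Quality of Life Index for Spinal Cord Injury (QLI-SCI". In section 6.2 the baseline visit asks staff to "administer ASIA impairment scale assessment (an objective scoring system to document level of spinal cord injury", and the follow-up visits again list the impairment scale, FIM and QLI-SCI. Appendix 1 has one row for each of the three instruments and none for an ASIA motor score, sensory score or neurological level. Section 8.3 plans linear and logistic regression, "evaluating the relationship between the physiologic parameters with: ASIA, FIM and QLI-SCI functional outcome metrics".

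Eligibility (section 5.1) is "patients with acute traumatic spinal cord injury ASIA A, B or C".

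Two other neurological items appear:

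- **Motor evoked potentials.** Section 4.3, for patients being evaluated for this monitoring, says "we will capture transcranial magnetic motor evoked potentials within the 24 hours pre-operatively, 24hrs post-operatively", and again at the functional assessments. Secondary hypothesis 3 in section 3.1 expects time near optimal SCPP to be "directly associated with improved motor evoked potentials and functional outcomes", in incomplete injury. Section 8.3 analyses them; the outcome list in 3.2 does not mention them.
- **Neurological injury.** Section 3.2 lists it among the adverse events, with no scale or threshold.

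**The concern.** Secondary objective 2 asks whether SCPP is related to outcome in about 20 patients. Its one clinical neurological measure has few steps and a floor occupied by part of the cohort. A complete patient who loses a level stays at grade A. A grade C patient who gains strength without reaching the next grade stays at C. Both are recorded as unchanged.

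The wording adds to the difficulty. The baseline visit describes the impairment scale as recording level, whereas the grade records severity, and section 8.3 says only ASIA. Staff cannot tell from the protocol whether grade, level or scores are to be entered. This belongs in the protocol, because a score not written down at baseline and follow-up cannot be recovered by a later analysis plan.

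**Working it through.** **Plan's own figure.** There is none to reproduce. The 20 patients (section 4.1) are what two years of recruitment is expected to yield, and no power, effect size or dropout is given. Alpha is 0.05 (section 8.1); two-sided testing is assumed here.

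**Assumption about the scale.** The protocol does not describe how the scale is built. Taken as general knowledge: A is the complete, bottom grade; the grade records severity; and the motor score, sensory scores and level come from the examination used to assign it.

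**Step 1, coverage.** Who is covered by each neurological measure:

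| Measure | Where | Coverage | Can it show worsening in grade A? |
|---|---|---|---|
| ASIA grade | 3.2, 4.4, 6.2, 8.3 | all patients | No |
| Motor evoked potentials | 3.1, 4.3, 6.2, 8.3 | those evaluated for them; objective 3 is incomplete injury only. The daily visits in 6.2 list the test without that limit | Not clear that grade A is covered |
| Neurological injury (adverse event) | 3.2 | all patients | Yes, but with no measure attached |
| ASIA motor score, sensory scores, level | not named | none specified | Would allow it |

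**Step 2, floor.** The share of grade A is not stated. Assuming 30% to 70%: 20 × 0.3 = 6 and 20 × 0.7 = 14 patients who cannot worsen on the grade.

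**Step 3, coarseness (objective 2 only).** Exposure and true recovery were simulated as bivariate normal with N = 20. Recovery was either used directly as an error-free score or cut into grade-change categories. The correlations and cut points are assumptions.

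- Pearson test, 6,000 runs, 20-40% improving at least one grade and 3-10% two.
- Spearman test, 8,000 runs, four splits from 80/20 (unchanged / at least one grade better) to 50/30/20, one of them with 5% worsening.

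| Assumed correlation | Pearson: score vs grade | Spearman: score vs grade |
|---|---|---|
| 0.4 | 0.43-0.44 vs 0.23-0.32 | 0.37-0.38 vs 0.21-0.32 |
| 0.5 | 0.64-0.65 vs 0.34-0.48 | 0.56-0.58 vs 0.31-0.47 |
| 0.6 | 0.83-0.84 vs 0.48-0.67 | 0.76-0.77 vs 0.45-0.67 |

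**Step 4, measurement error.** If the score has reliability 0.8, Pearson power at correlation 0.5 falls to about 0.54. At 0.7 the observed correlation is 0.5 × √0.7 = 0.42 and power is about 0.47, level with the best grade-change case.

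**Step 5, what N = 20 can detect.** The correlation detectable with 80% power is tanh((1.960 + 0.842)/√(20 − 3)) = tanh(0.680) = 0.59, even for an error-free score.

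**The case against.** Several stronger readings are tempting, and the protocol does not support them.

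- **That the grade is the only neurological outcome.** It is not: motor evoked potentials are an outcome in hypothesis 3 and are analysed in 8.3. This stands, so the point is confined to clinical examination.
- **That the ASIA scores are collected and thrown away.** The protocol says neither that they are recorded nor that they are discarded. The baseline visit calls the assessment a scoring system, 8.3 says only ASIA, and the case report forms are not shown. What can be said is that the scores are not specified as outcomes.
- **That probe damage in a grade A patient would go unseen.** Neurological injury is a separate safety event, adverse events are documented at daily visits, and a committee reviews them after every five patients. The grade is not the safety measure. What remains is that this event has no measure attached.
- **That the perfusion-outcome analyses as a whole lose much of their power.** FIM and QLI-SCI also serve objective 2, and motor evoked potentials serve objective 3. The floor does not bear on objective 3, which excludes complete injury. With an assumed 10 incomplete patients and correlation 0.5, power is about 0.32 with a continuous score and 0.16-0.22 with grade change, which is inadequate either way. The simulated loss reflects coarseness, not the floor.
- **That the motor score should replace the grade.** Enrolment runs from C0 to L1, and the motor score has no key muscles for thoracic segments. A complete thoracic patient could lose a level with no change in motor score.

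It is also fair to say that these are secondary outcomes in a 20-patient feasibility and validation study that makes no power claim.

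**Conclusion.** The point holds in a limited form. No figure in the protocol is wrong. The outcome set leaves grade A patients without a specified clinical measure that can fall, and leaves change within a grade unrecorded as an outcome for everyone. The description of the scale as documenting level needs correcting whichever measure is preferred.

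The floor affects 6 to 14 of 20 patients if 30-70% are grade A. The gain in power for objective 2, about 0.56-0.65 against 0.31-0.48 at an assumed correlation of 0.5, is an upper bound: it rests on assumed correlations and conversion rates and on an error-free score, and could vanish at a reliability of 0.7. It does not make the study well powered, and no gain is claimed for objective 3. The change is worth making because it is cheap and cannot be made retrospectively if the scores were never recorded.

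**What to change.** 1. In sections 3.2, 4.4 and 6.2 (baseline and follow-up visits) and Appendix 1, specify that the total motor score, sensory scores and neurological level are recorded from the ASIA examination already performed, together with the grade. Correct the baseline wording so that grade and level are separate items. List motor evoked potentials in 3.2, stating in whom they are measured.
2. In section 8.3, replace the bare reference to ASIA with the follow-up motor and sensory scores, adjusted for their baseline values, analysed alongside grade conversion. For thoracic injuries, rely on sensory score and level.
3. Under safety, report loss of neurological level or score from baseline descriptively, so that worsening in grade A patients can be seen.

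Cost: a few extra fields on the existing form and a few extra analyses, with no additional examination. The added analyses are further secondary comparisons in a small sample and should be presented as such.
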